## Abstract

**Background:**

The Subacromial Impingement Syndrome (SIS) is the most common diagnosed disorder of the shoulder in primary health care, but its aetiology is unclear. Conservative treatment regimes focus at reduction of subacromial inflammatory reactions or pathologic scapulohumeral motion patterns (*intrinsic *aetiology). Long-lasting symptoms are often treated with surgery, which is focused at enlarging the subacromial space by resection of the anterior part of the acromion (based on *extrinsic *aetiology). Despite that acromionplasty is in the top-10 of orthopaedic surgical procedures, there is no consensus on its indications and reported results are variable (successful in 48-90%). We hypothesize that the aetiology of SIS, i.e. an increase in subacromial pressure or decrease of subacromial space, is multi-factorial. SIS can be the consequence of pathologic scapulohumeral motion patterns leading to humerus cranialisation, anatomical variations of the scapula and the humerus (e.g. hooked acromion), a subacromial inflammatory reaction (e.g. due to overuse or micro-trauma), or adjoining pathology (e.g. osteoarthritis in the acromion-clavicular-joint with subacromial osteophytes).

We believe patients should be treated according to their predominant etiological mechanism(s). Therefore, the objective of our study is to identify and discriminate etiological mechanisms occurring in SIS patients, in order to develop tailored diagnostic and therapeutic strategies.

**Methods:**

In this cross-sectional descriptive study, applied clinical and experimental methods to identify intrinsic and extrinsic etiologic mechanisms comprise: MRI-arthrography (eligibility criteria, cuff status, 3D-segmented bony contours); 3D-motion tracking (scapulohumeral rhythm, arm range of motion, dynamic subacromial volume assessment by combining the 3D bony contours and 3D-kinematics); EMG (adductor co-activation) and dynamometry instrumented shoulder radiographs during arm tasks (force and muscle activation controlled acromiohumeral translation assessments); Clinical phenotyping (Constant Score, DASH, WORC, and SF-36 scores).

**Discussion:**

By relating anatomic properties, kinematics and muscle dynamics to subacromial volume, we expect to identify one or more predominant pathophysiological mechanisms in every SIS patient. These differences in underlying mechanisms are a reflection of the variations in symptoms, clinical scores and outcomes reported in literature. More insight in these mechanisms is necessary in order to optimize future diagnostic and treatment strategies for patients with SIS symptoms.

**Trial registration:**

Dutch Trial Registry (Nederlands Trial Register) NTR2283.

## Background

### Introduction

The Subacromial Impingement Syndrome (SIS) can be defined as symptomatic irritation of the rotator cuff and subacromial bursa in the limited subacromial space. Clinical characteristics are pain with arm abduction (painful arc), decreased active range of motion (RoM) and loss of arm force and function [1-5]. It is the most frequently diagnosed shoulder disorder in primary health care, accounting for 44-65% of all shoulder complaints [3,6]. Symptoms can persist for months or years and the majority of patients are between 40 and 50 years old. Consequently, SIS has a significant socioeconomic impact [7].

Despite its reported prevalence, the diagnostic criteria and aetiology of SIS are debatable. Two main etiologic theories have been described. Neer's widely accepted impingement theory focuses on the *extrinsic *mechanism: symptoms result from compressive forces on the rotator cuff, caused by biomechanical or structural anatomic (bony) abnormalities [8,9]. The mechanisms leading to this assumed compression remain unclear. Scapula dyskinesia, causing relative cranial translation of the humerus, has been reported [6,10-13]. Other studies describe a correlation between SIS and acromial shape (hooked acromion, Bigliani classification [14] type II or III) [4,15-18]. Presumably, this hooked acromion is a pre-existing anatomic variation or a traction spur on the coracoacromial ligament caused by repetitive cranially directed translations of the humerus or by tendinopathy. Others conclude there is no relation between acromial shape and SIS, or underline the difficulties in using acromial shape as an assessment tool [16,19,20]. The majority of partial rotator cuff tears, commonly referred to as a consequence or entity of SIS, are often either intratendinous or at the articular side of the rotator cuff and not at the bursal side where they would be expected if the rotator cuff 'impinges' against a hooked acromion [21]. Despite these unclarities, the extrinsic mechanism forms the rationale for one of the most frequently performed orthopaedic surgical procedures: acromionplasty. The second theory is based on a degenerative *intrinsic *mechanism: SIS can be caused by ischemia at the watershed zone of the supraspinatus tendon. This is enhanced by micro traumata or overuse, tensile overload on degenerating rotator cuff tendons, a subacromial inflammatory reaction, or insufficient cuff function leading to an imbalance between glenohumeral mobility and joint stability, with consequent glenohumeral destabilization or altered arm-shoulder kinematics [22-29]. Thirdly, SIS can be the consequence of adjoining pathologies or joint hyperlaxity. Furthermore, less classic forms of shoulder impingement, e.g. internal impingement and coracoid impingement have been described.

Treatment of SIS generally starts with conservative methods, including arm rest or physical therapy, non-steroidal anti-inflammatory drugs (NSAIDs) and subacromial corticosteroids injections. Conservative therapy is successful in 42% (Bigliani type III) to 91% (Bigliani type I) [30,31]. When conservative treatments fail, the classic surgical treatment of primary SIS is an acromionplasty as described by Neer [8,9]. Variable and often mediocre results of this frequently applied procedure have been reported, with success rates ranging from 48 to 90% [32-36]. However, acromionplasty doesn't affect continuing degeneration of the rotator cuff [37], and subacromial spur recurrence has been reported following acromionplasty [21,38,39]. Henkus et al. reported comparable results for acromionplasty and bursectomy in patients with SIS [40]. This is in concordance with other studies that also report clinical improvements in SIS-patients without changing the coracoacromial shape [31,40-44].

Although SIS has been typically assumed to be the result of rotator cuff injury, the subacromial space is a complex anatomical environment, containing several structures that can be a source of pain. Even several pathologies that have a similar patients' history, pain patterns and findings with physical examination, can be (mistakenly) diagnosed as SIS [45]. In a recent study at our institution, 14 of 80 patients (17.5%) clinically diagnosed with SIS, had to be excluded following MRI arthrography because of alternative shoulder pathology [40].

Concluding, the ongoing debate on the aetiology of SIS, its varying clinical presentations, the diagnostic difficulties and the highly variable treatment outcomes of SIS suggest there might be multiple pathophysiologic mechanisms leading to complaints clinically diagnosed as SIS that need specific approaches in clinical practice.

### Hypothesis

The extrinsic pathophysiologic mechanism is only valid for a subgroup of SIS patients, and consequently acromionplasty is the wrong treatment for at least a part of the patients suffering from SIS symptoms. The complaints observed in SIS are presumably a compilation of symptoms that originate from different shoulder pathologies and etiologic mechanisms. It is our challenge to discriminate these intrinsic and/or extrinsic underlying aetiologies.

We developed a theoretical framework for the aetiology of impingement ("a disbalance between subacromial volume and the space needed for subacromial structures", i.e. increased subacromial pressure) based on 4 distinct proposed mechanisms (Figure 1):

**Figure 1 F1:**
[figure not shown]
**A. Schematic anatomy of a healthy glenohumeral joint and subacromial space. B. Schematic anatomy of a shoulder joint with the presence of several etiologic mechanisms for Subacromial Impingement Syndrome.** In theory, impingement ("a disbalance between acromial space and the space needed for subacromial structures") can be caused by 1) A dynamically reduced subacromial space due to a pathologic pattern of arm-shoulder movements (e.g. scapular dyskinesia), resulting in relative cranialisation of the humerus with respect to the scapula/acromion, or 2) A more statically reduced subacromial space, due to 2a) structural anatomic variations (e.g. a hooked acromion), eventually in combination with altered arm-scapula motion patterns; 2b) A subacromial inflammatory reaction (e.g. caused by micro-trauma or overuse) causing subacromial oedema, fibrosis and tendinosis; 2c) Encroachment of subacromial tissues by an adjoining pathology or structures other than the acromion (e.g. acromioclavicular (AC)-joint osteoarthritis and subacromial osteophytes, calcifying tendinitis, and coracoid impingement).

1) A dynamically reduced subacromial space due to a pathologic pattern of arm-shoulder movements (e.g. scapular dyskinesia), resulting in relative cranialisation of the humerus with respect to the scapula/acromion.

2) A more statically reduced subacromial space, due to:

a. structural anatomic variations (e.g. a hooked acromion), eventually in combination with altered arm-scapula motion patterns;

b. a subacromial inflammatory reaction (e.g. caused by micro-trauma or overuse) causing subacromial oedema, fibrosis and tendinosis;

c. Encroachment of subacromial tissues by an adjoining pathology or structures other than the acromion (e.g. acromioclavicular (AC)-joint osteoarthritis and subacromial osteophytes, calcifying tendinitis, and coracoid impingement).

In this study, factors associated with these SIS mechanisms will be analyzed in patients clinically diagnosed with SIS. As a result, SIS patients will be categorised in "dynamic" and "static" etiologic subgroups, each requiring tailored diagnostics and treatment strategies.

Because subacromial impingement syndrome is a clinical diagnosis, possible other causes of shoulder pain and SIS symptoms (e.g. early stage frozen shoulder, calcifying tendinitis, slap lesions, rotator cuff tears, etc.) are identified and, if eligible, analyzed separately in distinct research projects (trial registry numbers: NTR1545 and NTR2282).

### Study goals

#### Primary goal

Identification and classification of distinct pathophysiological mechanisms for symptoms clinically diagnosed as SIS into identifiable subgroups of patients as categorized above, in order to design tailored concept diagnostics and treatment flowcharts from experimental concepts.

#### Secondary goals

A set of experimental and diagnostic tools is combined to identify structural and biomechanical etiological factors in SIS patients, which will be related to clinical and functional status:

A. Presence and severity of pathologies in the subacromial space with MRI, e.g. (partial) cuff-ruptures, tendinosis, fibrosis or a subacromial inflammatory reaction, and assessment of cuff degradation status.

B. Acromial shape classification and 3D shape parameters of the humerus, scapula and subacromial space volume, using conventional radiographs and segmented MRI-arthrographies.

C. Quantification of cranialisation of the humerus with respect to the scapula at rest and during active arm abduction and adduction tasks with simultaneously acquired shoulder radiographs and Electromyography (EMG) recordings (see D).

D. Measurements of the activation of arm adductors during arm abduction tasks and assessment of the presence of arm adductor co-activation (Activation Ratio).

E. Analyses of 3D-kinematics (arm range of motion and scapulohumeral rhythm) of the affected SIS shoulder compared to the unaffected shoulder and eventual etiologic SIS subgroups, with the use of 3D motion registration.

F. Changes in reconstructed subacromial volume and acromiohumeral distance during arm abduction by combining the recorded 3D-kinematics with the MRI-segmented 3D bony shapes.

G. The effect of a subacromial infiltration of lidocaïne on arm range of motion, scapulohumeral and -thoracic rhythm with arm abduction, reconstructed subacromial volume and muscle activation patterns, including adductor co-activation.

H. Biomechanical analyses of structural or coordinative muscular imbalance by means of model simulation (Delft Shoulder and Elbow Model) with recorded 3D-kinematics as input.

I. Clinical phenotyping, using validated clinical scores and questionnaires.

J. Identification of alternative diagnoses that may cause complaints clinically diagnosed as SIS, using MRI and radiographs (e.g. acromioclavicular-osteoarthritis and subacromial osteophytes, calcifying tendinitis, SLAP lesion or coracoid impingement).

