#### 3D kinematics and changes in subacromial volume (E, F, G)

Range of Motion (RoM) and 3D motions of forearm, humerus and scapula with respect to the thorax will be recorded by means of an electromagnetic tracking system: 'Flock of Birds' (FoB, Ascension Technology Corp, Burlington, VT, USA) and custom made computer software (FOBVis, Clinical Graphics, Delft, the Netherlands). The FoB obtains 3D kinematical data using sensors on thorax, scapula, humerus, forearm and thorax. After palpatory identifying three dimensional positions of standard bony landmarks of the arm, shoulder and thorax with respect to the sensors for each patient, local bone coordinate systems are created, based on the subject's individual anatomy. The glenohumeral rotation centre is estimated from the position of five scapular bony landmarks using linear regression [61]. The RoM of the following movements is measured: anteflexion, retroflexion, abduction in frontal plane, internal rotation in 0 and 90 degrees of arm abduction and external rotation in 0 and 90° of arm abduction.

3D kinematics and MRI bony segmentation (3D shape parameters of scapula and humerus) will be combined in custom made computer software (Articulus, Clinical Graphics, Delft, the Netherlands) to reconstruct the subacromial space volume and AH during recorded humerus elevations, allowing dynamic measurements of patient-specific subacromial space characteristics [5,62,63]. Additionally, the effect of a subacromial lidocaïne injection on RoM, scapulohumeral rhythm, reconstructed AH and subacromial volume of the affected shoulder will be analyzed.

*Main kinematic outcome parameters*: Passive and active RoM during standardized arm motions (with and without subacromial anaesthetics) of both arms; Scapulohumeral rhythm of affected and healthy arm; Reconstructed changes in AH and subacromial volume during dynamic arm abduction (combining MRI-based shape parameters and 3D RoM measurements).

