#### Statistical analyses

Patient data, including patient characteristics, physical examination, interview, radiological findings, questionnaires, psychological scores, biomechanical measurements and MRI findings will be entered in a database.

With regards to presence of cranial translation of the humerus as detected on radiographs during rest and abduction and adduction tasks, statistical analysis will be performed by a means of repeated measures ANOVA, with the measure of co-contraction controlled as a confounding factor.

For the isometric Principal Action EMG measurements, data are tested by means of a General Linear Model analysis for repeated measures, controlling for factors Muscle, subacromial anaesthetics, sAH and VAS for pain.

RoM in standardized motions will be analyzed with a General Linear Model analysis for repeated measures, controlling for factors VAS pain, subacromial anaesthetic, dAH and sAH. dAH obtained from 3D-kinematics will be analyzed equally.

Additionally, we will use students' unpaired t-tests to compare continuous variables (e.g. patient characteristics, clinical scores, RoM, dAH) between defined pathologic subgroups.

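### The unaffected arm is the reference for range of motion and scapulohumeral rhythm, but arm dominance is in no stated factor list, so the side contrast can carry a dominance difference

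*Protocol article*

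**What the plan says.** Goal E in the Secondary goals section names two comparators for the affected shoulder's kinematics, the aetiological subgroups and the patient's other shoulder: "Analyses of 3D-kinematics (arm range of motion and scapulohumeral rhythm) of the affected SIS shoulder compared to the unaffected shoulder". The section on 3D kinematics and changes in subacromial volume lists RoM of both arms and "Scapulohumeral rhythm of affected and healthy arm" among its main outcomes. Selection of participants requires unilateral pain and a symptom-free opposite shoulder. No healthy control group is described, so the opposite arm is the only reference without SIS for these measures.

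The Statistical analyses section states control factors model by model:
- Cranial translation on radiographs: repeated-measures ANOVA "with the measure of co-contraction controlled as a confounding factor".
- Principal Action EMG: a general linear model "controlling for factors Muscle, subacromial anaesthetics, sAH and VAS for pain".
- RoM: a general linear model for repeated measures "controlling for factors VAS pain, subacromial anaesthetic, dAH and sAH".

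Subgroups are then compared on continuous variables, RoM among them, by unadjusted unpaired t-tests. Neither arm dominance nor handedness is mentioned anywhere in the article.

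**The concern.** A patient's other arm is a fair control only if the two arms would be alike without disease, or if the affected side is the dominant one in half of the patients, or if dominance is adjusted for. The article's own theory gives some reason to doubt an even split. One proposed mechanism is "A subacromial inflammatory reaction (e.g. caused by micro-trauma or overuse"), and it is a modest inference, though not a statement of the article, that overuse falls more on the dominant arm.

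If so, a normal difference between dominant and non-dominant arms would appear in goal E as an effect of SIS. If the share with the dominant arm affected also differs between subgroups, part of a subgroup difference in RoM would reflect dominance and not mechanism. Adding side to the model would not cure this, because side and dominance would still be mixed. If dominance is not recorded, no later analysis can adjust for it.

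**Working it through.** **Inputs from the article.** n = 100 patients (Sample size); one affected shoulder per patient (Selection of participants); unadjusted unpaired t-tests between subgroups (Statistical analyses). The article states no figure on dominance, so there is none to reproduce.

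**Assumed inputs.**
- p, the share of patients whose dominant arm is affected: 0.5, 0.7, 0.8.
- d, the dominant-minus-non-dominant difference: 2 to 5 degrees.
- SD of the side difference apart from dominance: 10 degrees.
- True SIS effect: zero.

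**Step 1, bias of the side contrast.** Affected minus unaffected equals the SIS effect + d when the dominant arm is affected, and the SIS effect - d otherwise. The mean is therefore the SIS effect + p x d - (1 - p) x d = the SIS effect + (2p - 1) x d.
- p = 0.5: 0.
- p = 0.7: 0.4 x 2 = 0.8 to 0.4 x 5 = 2.0 degrees.
- p = 0.8: 0.6 x 2 = 1.2 to 0.6 x 5 = 3.0 degrees.

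**Step 2, false rejection.** The variance of the side difference is 10² + 4 x d² x p x (1 - p). The noncentrality is the bias x √100 / SD, for a two-sided paired t-test at 0.05.

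| p | d (degrees) | bias (degrees) | SD (degrees) | noncentrality | rejection |
|---|---|---|---|---|---|
| 0.5 | 2 or 5 | 0 | 10.20 or 11.18 | 0 | 5.0% |
| 0.7 | 2 | 0.8 | 10.17 | 0.79 | 12.2% |
| 0.7 | 5 | 2.0 | 11.00 | 1.82 | 43.7% |
| 0.8 | 2 | 1.2 | 10.13 | 1.18 | 21.7% |
| 0.8 | 5 | 3.0 | 10.77 | 2.79 | 78.8% |

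**Step 3, subgroup contrasts.** For RoM of the affected arm, each subgroup mean contains its own share times d, so the contrast is off by (p1 - p2) x d. With 0.8 versus 0.5 this is 0.3 x 2 = 0.6 to 0.3 x 5 = 1.5 degrees. If side differences are compared instead, the error is 2 x (p1 - p2) x d, or 1.2 to 3.0 degrees. Both are zero when dominance is spread equally over the subgroups.

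**Step 4, lidocaine contrasts.** Before and after are measured on the same arm, so the dominance term cancels.

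**The case against.** The strongest reply has four parts.

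First, a condensed article need not list every recorded characteristic or covariate; patient characteristics go into the database without being itemised, and dominance may be among them. That is possible. But the article does state control factors for its models and names one confounder outright, and the list that can be read lacks the factor most closely tied to a side-to-side comparison.

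Second, the RoM factor list ("controlling for factors VAS pain, subacromial anaesthetic, dAH and sAH") does not include side, so it may describe the lidocaine analysis of the affected arm and not goal E. This stands: the article gives no explicit model for the side contrast. It limits the point to a contrast analysed without dominance, as everything written suggests it would be.

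Third, nothing in the article says that dominance alters RoM or rhythm, or that p exceeds one half. This also stands. p, d and the SD are assumptions, one degree scale serves two different measures, and the rejection rates range widely.

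Fourth, a reader might infer that the primary classification is thereby wrong, since altered scapulohumeral rhythm is a marker of the dynamic subgroup. The article does not support that. Altered rhythm is one of six listed markers, it is also expected in subgroups 2a and 2b, and no side-difference cut-off is given for calling a rhythm altered. A correction patient by patient would need normal reference values for side differences, which the study does not describe collecting.

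**Conclusion.** The concern holds in conditional form. The opposite arm is the only reference without SIS for RoM and scapulohumeral rhythm, no stated factor list includes dominance, and an unadjusted side contrast is then biased by (2p - 1) x d. The algebra is exact; the size is not known from the article. Under the assumptions above the bias runs from none at p = 0.5 to 3.0 degrees at p = 0.8 with d = 5. Subgroup comparisons of affected-arm RoM are exposed only if dominance differs between subgroups, and by half as much as comparisons of side differences.

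It does not follow that dominance differences will certainly be read as effects of SIS or of a mechanism: that needs an uneven split and a real difference between arms. The point bears on goal E and on subgroup comparisons of the same measures. It leaves the lidocaine contrasts untouched and does not show any patient to be misclassified.

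**What to change.** Record which arm is dominant. In the affected-versus-unaffected comparison of RoM and scapulohumeral rhythm, include an indicator for dominant arm affected, coded +0.5 / -0.5. In a model for the side difference the intercept is then the side effect at balanced dominance, and the coefficient of the indicator estimates 2d. Adjust subgroup comparisons of these measures for the same indicator.

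The cost is one recorded item and one degree of freedom, with no added procedure. There is some loss of precision when p is far from one half: the standard error of the adjusted side effect is 10 / √(4 x 100 x p x (1 - p)), or 1.09 degrees at p = 0.7 and 1.25 at p = 0.8, against 1.02-1.10 and 1.01-1.08 unadjusted (the SDs in the table divided by √100). If SIS itself acts differently on dominant and non-dominant arms, the indicator absorbs that too, and the adjusted effect is the equally weighted average of the two; the report should say so.
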